#### Rejection criteria

4.6.5

1.Those who do not to meet either the inclusion or exclusion criteria after enrollment;2.Those who have not used the medicines according to the regulations, cannot judge the curative effect or provide incomplete information;3.Those who have consumed drugs that are forbidden and may influence the judgment of effection;4.Those who have acute infection during the test

#### Exit criteria

4.6.6

1.Poor effection, along with the subject not following through with the complete treatment course;2.Presence of adverse reactions that are difficult to tolerate, resulting in the subject leaving the study;3.Occurrence of serious adverse events (AEs);4.Complications associated with other diseases during the trial deeming the participant unsuitable to continue the test;5.Subjects withdrawing from the trial without an explanation

#### Suspension criteria

4.6.7

1.Occurrence of serious safety problems during the test;2.Suspension ordered by the administrative department.

Researchers should strive to contact the participants to ascertain the reasons for dropping out from the study, and to acquire other relevant information such as the last time that they had taken the decoction, and to convince them to finish the examinations as far as they possibly can. If the participants experience any AEs during the study, researchers should provide appropriate treatment for them. The expected dropout rate should be <15%. The dropout cases will be included in the statistical analysis.

### Follow-up

4.7

#### Participant timeline

4.7.1

Screening, intervention, and assessment visits will be performed by a researcher. The schedule of visits and measurements is given in Figure 1 in compliance with Standard Protocol Items: Recommendations for Interventional Trials (SPIRIT) figure.

**Figure 1 F1:**
[figure not shown]
The schedule of visits and measurements.

Screening period: 2 weeks prior to the intervention. Intervention period: 8 weeks. Follow-up period: 24 weeks after the intervention.

### Outcome measures

4.8

#### Primary outcomes

4.8.1

1.Arterial color Doppler ultrasound. (Assess arterial intimal thickness, degree of sclerosis, plaque, stenosis)^[16,17]^

Arterial color Doppler ultrasound will be tested at Visits 0 and 8.

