#### Traditional Chinese medicine intervention

4.5.3

All participants in the treatment group will visit the researchers once every month, when the same Chinese doctor will examine them using four TCM diagnostic methods including inspection, listening and smelling, inquiry, and pulse measurement and palpation. Shenqi compound is composed of 8 Chinese herbs: ginseng, astragalus, raw radix rehmanniae, trichosanthin, dogwood, yam, salvia, and wine rhubarb. Ginseng and astragalus supplement the vitality together as the remedy. The four medicines are used in cooperation with each other to supplement the deficiency of yin and jin of the lungs, spleens, and kidney. Salvia miltiorrhiza and wine rhubarb are used as adjuvants to promote blood circulation and remove blood stasis. Shenqi compound regulates the body's energy metabolism and reduces blood glucose fluctuation, which is a good recipe for clinical treatment of type 2 diabetes with lower extremity atherosclerosis. At present, it has been included in the “Diagnosis and Treatment Program for Diabetes” of the Chinese Traditional Medicine Clinical Research (Diabetes) Base. The test drug is a Chinese medicine formula granule produced by Sichuan Green Pharmaceutical Technology Development Co., Ltd. Certification and quality control by director of the department of pharmacy department in the Teaching hospital of Chengdu University of TCM. Usage instructions suggest consuming the granules three times a day one lattice each time, by boiling with water before meals, stirring, covering, and sealing for 3 to 5 min. The main ingredients of placebo are beta-cyclodextrin and artificial food colors. Shenqi compound and placebo are both fried-free granules, are similar in packaging, appearance, and shape. Participants are not allowed to take other drugs during the 8-week study period. Each participant will receive 28 boxes of Chinese medicine formula granules. Participants will be asked to record the changes in their symptoms daily using a form reviewed by a researcher once every month.

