#### Secondary outcomes

4.8.2

1.Measurement of blood glucose levels before three meals, 2 h after three meals, and before sleeping; calculation of average blood glucose levels (MBG), standard deviation of mean blood glucose (SDBG), and maximum blood glucose fluctuation (LAGE).2.β-cell function evaluation index: insulin resistance index (HOMA-IR), area under the glucose curve (SG), and area under the C-peptide curve (SCP). Calculating HOMA-IR, SG, and SCP by:Homa-IR (CP) = 1.5 + G 0 min × CP 0 min/2800; Homa-islet (CP) = 0.27 × CP 0 min/(G 0 min − 3.5);SG = (G 0 min + G 180 min)/2 + G 30 min + G 60 min + G 120 min;SCP = (CP 0 min + CP 180 min)/2 + CP 30 min + CP 60 min + CP 120 min;(G 0 min to G 180 min, CP 0 min to CP 180 min, respectively means blood glucose and C-peptide values at each time point after Steamed bun test).^[18,19]^Blood glucose will be tested at visits 1, 3, and 5. β-cell function evaluation index will be tested at visits 1 and 5.3.Blood lipid: total cholesterol (TC), triglyceride (TG), high density lipoprotein cholesterol (HDL-C), and low density lipoprotein cholesterol (LDL-C);4.Inflammation indicators (NLR, IL-6, and CRP)5.HbA1c

Blood glucose will be tested at visits 1, 3, and 5. β-cell function evaluation index, HbA1c, inflammation indicators and blood lipid will be tested at visits 1 and 5.

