#### Life quality index

4.8.3

Using the assessment scale for the patient's quality of life (SF-36 scale Chinese version) is used.

All life quality assessment scales will be tested at visits 1, 3, 5, 6, and 7.

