#### Blood samples

4.9.2

Blood samples will be collected after fasting overnight, including blood glucose levels (baseline, w4, w8), postprandial C peptide and glucose levels at 0.5, 1, 2, and 3 h (baseline, w8), along with HbA1c and blood lipid (baseline, w8). The kit is provided by Depp. Blood samples will be sent to the laboratory of Teaching Hospital of Chengdu University TCM for analysis.

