Compared to other studies, this study focuses on influencing blood glucose fluctuations and improving lower extremity atherosclerosis. Here, we want to further study the efficacy of Shenqi Compound in influencing the blood glucose fluctuation in type 2 diabetes with lower extremity atherosclerosis. Since blood glucose fluctuations are prone to damage the vascular endothelium and are a risk factor for lower extremity atherosclerosis,^[21]^ the effect of Shenqi Compound on arterial color Doppler ultrasound is evaluated as the main outcome indicator. Because blood glucose fluctuations are important predictors of vascular complications of diabetes,^4^ the evaluation of blood glucose fluctuations and islet β-cell function indicators will be calculated by formulae as secondary outcome indicators. Since HbA1c variability represents long-term blood glucose fluctuations,^[3]^ the effect of Shenqi compound on glycated hemoglobin is also evaluated. Furthermore, blood glucose fluctuation and lower extremity atherosclerosis are closely related to disorders of lipid metabolism,^[22]^ it is also imperative to evaluate the effects of Shenqi compound on blood lipids. Inflammatory cells play an important role in the occurrence and development of lower extremity atherosclerosis, due to which NLR is closely related to the formation of AS, subsequently highlighting the need to the effect of Shenqi compound on inflammation indicators, specifically NLR. Evaluating the severity of lower extremity atherosclerosis by detecting NLR clinically would be essential in providing a powerful reference for the refinement and management of patients.^[7]^ Bias will be minimized by adopting a rigorous methodology. Despite the fact that this study is an open label trial, some measures will be considered to strengthen quality control, considering the nature of RCT multicenter trial and CER design. To avoid the bias from the researchers, an independent investigator will be assigned in each research center as the contact person to preserve and record the randomization information. Therefore, clinical researchers will have no influence on enrollment or randomization. This study strives to effectively improve the blood glucose fluctuation and delay type 2 diabetes with lower extremity atherosclerosis, which has significant social benefits.

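### The primary outcome is a scan with four unranked features and no deciding variable, and the text's visit numbering places its only post-baseline reading after treatment ends

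*Protocol article*

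**What the plan says.** All references are to the Protocol article.

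- **Outcome.** Section 4.8.1 has one entry, the ultrasound scan, with the bracketed instruction "Assess arterial intimal thickness, degree of sclerosis, plaque, stenosis". The Discussion again names only the scan: "the effect of Shenqi Compound on arterial color Doppler ultrasound is evaluated as the main outcome indicator".
- **Scan times.** "Arterial color Doppler ultrasound will be tested at Visits 0 and 8".
- **Analysis.** Section 4.9.8 assigns the t test to measurement data, chi-square to counts and rank-sum to ranked data. It refers to the main variables in the plural and says only which analysis sets they are run on. It gives no significance level.
- **Sample size.** Section 4.5.7 uses SDBG, which section 4.8.2 lists as secondary. It gives no difference, SD or event rate for any ultrasound feature.
- **Visit numbering.** Section 4.8.2: "Blood glucose will be tested at visits 1, 3, and 5". Section 4.9.2 gives the same measurement in weeks: "including blood glucose levels (baseline, w4, w8". Section 4.8.3: "All life quality assessment scales will be tested at visits 1, 3, 5, 6, and 7".
- **Period lengths.** Section 4.4 gives 4 weeks of test drug and then 8 weeks of observation. The Abstract, the Figure 1 legend and the Discussion give 8 weeks and then 24.

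**The concern.** The primary outcome section names an instrument, not a variable. Thickness is naturally continuous, sclerosis and stenosis may be graded, and plaque may be present or absent, so the analysis section could send them to different tests. No single comparison answers the trial's main question. If thickness improves and plaque does not, nothing in the protocol says whether the trial succeeded, and a favourable feature could be reported as the primary result after the data are seen. Blinding the analysts to group, as section 4.5.6 provides, does not supply the missing rule.

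The timing matters for interpretation. By the text's numbering, the primary is read once after baseline, in follow-up, and the other efficacy measures named above stop at week 8. The objective in section 4.1 does not say that the main question concerns an effect that persists after treatment.

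**Working it through.** **1. Does the sample size reveal the intended variable?**
Inputs from section 4.5.7: z values 1.64 and 1.28, σ = 2.41, δ = 2.0.
n per group = 2 × [(1.64 + 1.28) × 2.41 / 2.0]² = 2 × (3.5186)² = 24.76.
This reproduces the stated 24.76, hence 25 per group and 50 in total; 50 × 1.2 = 60. The figures all concern SDBG, so they do not identify an ultrasound feature.

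**2. Error rate with four unranked features.**
Assumptions, none of them stated in the protocol: each feature is tested once at two-sided 5%, any one significant feature may be claimed as primary success, and the four test statistics are equally correlated. The only 5% in the document is in section 4.5.7, where it is paired with the one-sided value 1.64.
If independent: 1 − 0.95⁴ = 0.185. For correlated tests, by simulation with 400,000 draws:

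| Assumed correlation | Chance of at least one false positive |
|---|---|
| 0 | 18.5% |
| 0.3 | 17.4% |
| 0.5 | 15.6% |
| 0.7 | 13.0% |
| 0.9 | 9.4% |

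Section 4.6.2 treats intima-media thickness above 1.2 mm as plaque, so thickness and plaque are linked by definition. Independence is therefore the upper end of the range and not the likeliest case.

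**3. What one named continuous variable could detect.**
With a 20% loss from 60, 48 remain, or 24 per group; the plan's own minimum is 25 per group. At two-sided 5% and 90% power, the detectable standardized difference is (1.960 + 1.282) × √(2/n):
- n = 24: 0.94
- n = 25: 0.92
- n = 30: 0.84

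Splitting 5% over four features (0.0125 each) raises the values for 24 and 25 per group to 1.09 and 1.07. Whether such differences are plausible cannot be judged, because the document gives no SD or expected change for any feature.

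**4. Where Visit 8 falls.**
Setting sections 4.8.2 and 4.9.2 side by side gives Visit 1 = baseline, Visit 3 = week 4, Visit 5 = week 8. Section 4.8.3 adds Visits 6 and 7. Visit 8 therefore comes after week 8.
If the five quality-of-life visits (1, 3, 5, 6, 7) match the five weeks in section 4.9.1 (baseline, 4, 8, 12, 24), Visit 7 is week 24 and Visit 8 is later. The end of follow-up, 8 + 24 = week 32, would fit, but this is an inference.
The lengths in section 4.4 give 4 + 8 = 12 weeks in total, which has no room for a week-24 assessment. After week 8 is after treatment under either set of lengths, but the gap from last dose to scan cannot be fixed from the text.

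**The case against.** The strongest objection is to the timing half. The schedule is in Figure 1, which is not reproduced in the copy reviewed, so a missing visit-to-week key is no fault of the plan. The visible text also allows a coherent reading. Visit 0 can be the screening visit in the 2 weeks before treatment, when a scan is needed for diagnosis, and Visit 8 a late follow-up visit. A primary read in follow-up is a design choice and not a contradiction. This stands. A reader might infer that the primary has no clear time, or that weeks 0 and 8 were certainly meant; the text supports neither.

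Other tempting extensions also fail:
- **Eight arteries as primary sites.** Section 4.6.2 lists the arteries as diagnostic criteria, and section 4.8.1 does not adopt them as outcome sites. Testing by artery would be conjecture.
- **Uncontrolled other treatment at the scan.** Section 4.5.3 says "Participants are not allowed to take other drugs during the 8-week study period", which might suggest free use afterwards. But section 4.6.5 rejects users of forbidden drugs with no time limit, and basic treatment is common to both arms.
- **18.5% as the error rate.** It needs independence and the any-one-wins rule. If all four features had to succeed, the error rate would not exceed 5%. The protocol states neither rule.

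One might add that an analysis plan could name the lead variable. But the protocol has its own primary outcome section, which fixes the outcome as a scan with four readouts, and the Discussion repeats it.

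**Conclusion.** The point holds on the primary variable. The protocol gives four unranked features, assigns tests by data type, sets no priority or multiplicity rule, and sizes the trial on a different outcome. Under the stated assumptions the chance of a false primary claim is about 9% to 18.5% instead of 5%. The exact figure depends on unknown correlations and on how success would be claimed. This should be fixed before any outcome data are seen.

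The timing part holds only in a narrow form. The text's numbering places the single post-baseline scan after treatment, later than the last reading of glucose, HbA1c, lipids and inflammation markers. The stated period lengths also conflict. The week of Visit 8 is not given in the text, and week 32 is not established. This part calls for clarification and does not by itself show an error in the choice of visit.

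**What to change.** 1. In section 4.8.1, name one ultrasound variable, one rule for the arterial site and side, and one test as primary. Change in intima-media thickness is an example; the choice is the investigators'. Make the other three features secondary.
2. In section 4.5.7, say that the sample size was set on SDBG and not on the named primary. A calculation for the new primary would need an SD and a target difference that the document does not contain.
3. In section 4.8.1, write the study week beside Visits 0 and 8. If week 8 was meant, correct the visit number. If a follow-up visit was meant, describe the primary as a post-treatment effect and give the interval since the last dose.
4. Reconcile the treatment and follow-up lengths in section 4.4 with those in the Abstract, the Figure 1 legend and the Discussion.

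The cost is protocol wording and an approved amendment. Naming one variable needs no extra scan. The downside is that three features lose primary status, and the trial must acknowledge that its power for the named variable is unknown. Keeping all four as primary at 0.0125 each would also control the error, but it raises the detectable standardized difference from about 0.92 to 1.07 at 25 per group.

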#### Secondary outcomes

4.8.2

1.Measurement of blood glucose levels before three meals, 2 h after three meals, and before sleeping; calculation of average blood glucose levels (MBG), standard deviation of mean blood glucose (SDBG), and maximum blood glucose fluctuation (LAGE).2.β-cell function evaluation index: insulin resistance index (HOMA-IR), area under the glucose curve (SG), and area under the C-peptide curve (SCP). Calculating HOMA-IR, SG, and SCP by:Homa-IR (CP) = 1.5 + G 0 min × CP 0 min/2800; Homa-islet (CP) = 0.27 × CP 0 min/(G 0 min − 3.5);SG = (G 0 min + G 180 min)/2 + G 30 min + G 60 min + G 120 min;SCP = (CP 0 min + CP 180 min)/2 + CP 30 min + CP 60 min + CP 120 min;(G 0 min to G 180 min, CP 0 min to CP 180 min, respectively means blood glucose and C-peptide values at each time point after Steamed bun test).^[18,19]^Blood glucose will be tested at visits 1, 3, and 5. β-cell function evaluation index will be tested at visits 1 and 5.3.Blood lipid: total cholesterol (TC), triglyceride (TG), high density lipoprotein cholesterol (HDL-C), and low density lipoprotein cholesterol (LDL-C);4.Inflammation indicators (NLR, IL-6, and CRP)5.HbA1c

Blood glucose will be tested at visits 1, 3, and 5. β-cell function evaluation index, HbA1c, inflammation indicators and blood lipid will be tested at visits 1 and 5.

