**Discussion::**

Explore the clinical effect of traditional Chinese medicine “Shenqi Compound” to reduce blood glucose fluctuation and use HOMA-IR, the area under the glucose curve, and the area under the C-peptide curve to evaluate the effect of protecting islet β cell function.

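### SG and SCP are called areas under the curve but weight unequally spaced samples as if equally spaced, and the β-cell index list is mislabelled and inconsistent

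*Protocol article*

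**What the plan says.** Section 4.8.2 (Secondary outcomes) lists three measures: "β-cell function evaluation index: insulin resistance index (HOMA-IR), area under the glucose curve (SG), and area under the C-peptide curve (SCP". The lead-in to the formulas, "Calculating HOMA-IR, SG, and SCP by", names the same three, but four formulas follow:

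- "Homa-IR (CP) = 1.5 + G 0 min × CP 0 min/2800"
- "Homa-islet (CP) = 0.27 × CP 0 min/(G 0 min − 3.5" (closing bracket follows in the text)
- "SG = (G 0 min + G 180 min)/2 + G 30 min + G 60 min + G 120 min"
- "SCP = (CP 0 min + CP 180 min)/2 + CP 30 min + CP 60 min + CP 120 min"

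G and CP are glucose and C-peptide in a steamed bun test. Section 4.9.2 (Blood samples) confirms the spacing after the fasting sample: "postprandial C peptide and glucose levels at 0.5, 1, 2, and 3 h", at baseline and week 8.

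The abstract Methods name four islet indicators, including Homa-islet. The abstract Discussion names HOMA-IR and the two areas as the means "to evaluate the effect of protecting islet β cell function", without Homa-islet. The main Discussion (section 5) says only that the indicators are computed by formula as secondary outcomes. No section states which direction of any index counts as benefit.

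**The concern.** There are two faults in the same item.

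**The formulas.** A trapezoid area gives each sample a weight equal to half the time between its neighbours (half the single gap at the ends). The printed weights would be right only if all four gaps were one hour. The first two gaps are half an hour, so the early part of each curve is over-weighted. SCP is a C-peptide measure that appears in every version of the list, so the fault touches the β-cell outcome as well as the glucose one. A treatment that changes the shape of the curve could be ranked wrongly.

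**The list.** An index that the protocol itself calls an insulin resistance index is filed as a measure of β-cell function. Homa-islet, the islet index for which a formula is printed, is missing from two of the three places where the measures are listed. HOMA-IR and Homa-islet can move in ways that carry opposite meanings, and no direction of benefit is given. A reader cannot tell which result would support the β-cell statement in the abstract Discussion.

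**Working it through.** The protocol gives no values for these indices, so it has no figure of its own to reproduce. The formulas and sampling times are taken from 4.8.2 and 4.9.2. All profiles and fasting values below are illustrative assumptions, with glucose in mmol/L and C-peptide taken as pmol/L.

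**1. Weights, in hours**

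| Sample | Stated weight | Trapezoid weight | Ratio |
|---|---|---|---|
| 0 min | 0.5 | 0.5/2 = 0.25 | 2 |
| 30 min | 1 | (0.5 + 0.5)/2 = 0.5 | 2 |
| 60 min | 1 | (0.5 + 1)/2 = 0.75 | 1.33 |
| 120 min | 1 | (1 + 1)/2 = 1.0 | 1 |
| 180 min | 0.5 | 1/2 = 0.5 | 1 |
| Sum | 4 | 3 | |

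The window is 3 hours, so proper weights must sum to 3. The ratio differs between rows, so the error is not one constant factor.

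**2. Two glucose profiles**

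Profile A: 8, 12, 15, 14, 10.

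- Stated SG: (8 + 10)/2 + 12 + 15 + 14 = 50.0
- Area: 0.25×8 + 0.5×12 + 0.75×15 + 1×14 + 0.5×10 = 2 + 6 + 11.25 + 14 + 5 = 38.25 mmol·h/L

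Profile B: 8, 10, 14, 16, 11.

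- Stated SG: (8 + 11)/2 + 10 + 14 + 16 = 49.5
- Area: 2 + 5 + 10.5 + 16 + 5.5 = 39.0 mmol·h/L

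B minus A is −0.5 on the stated formula and +0.75 on the true area, so the order reverses.

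**3. General form, for SG and SCP alike**

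If one curve is higher by x at 30 min and lower by x at 120 min than another, the stated sum does not change (x − x = 0). The true area falls by 0.5x (0.5x − 1.0x).

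**4. HOMA-IR against Homa-islet**

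HOMA-IR = 1.5 + G0×CP0/2800. Homa-islet = 0.27×CP0/(G0 − 3.5).

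- G0 = 8, CP0 = 600: HOMA-IR = 1.5 + 4800/2800 = 3.21; Homa-islet = 162/4.5 = 36.
- G0 = 8, CP0 = 750: HOMA-IR = 1.5 + 6000/2800 = 3.64; Homa-islet = 202.5/4.5 = 45.
- G0 = 6.4, CP0 = 750: HOMA-IR = 1.5 + 4800/2800 = 3.21, unchanged from the first case.
- G0 = 7, CP0 = 600: HOMA-IR = 1.5 + 4200/2800 = 3.00; Homa-islet = 162/3.5 = 46.3.

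At fixed fasting glucose, both indices rise with C-peptide. If lower HOMA-IR is read as better, the same change is worse on one index and better on the other. The direction holds over an assumed range of G0 from 7 to 11 and CP0 from 300 to 900: a 20% rise in C-peptide takes HOMA-IR from 2.25 to 2.40 at the low end and from 5.04 to 5.74 at the high end, while Homa-islet rises 20% everywhere. The third case shows that the opposition disappears once glucose falls enough. The fourth shows that a fall in glucose alone improves both indices.

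**The case against.** **The area error is largely a scale factor.** This is partly right. Profile A's stated SG exceeds its area by 31% (50.0/38.25), and most of that comes from weights summing to 4 instead of 3. Divided by total weight, A gives 50.0/4 = 12.5 against 38.25/3 = 12.75, a gap of 2%. A constant multiplier would not affect the planned t test. The unequal ratios remain, however. On the same per-weight basis B gives 12.375 against 13.0, so the reversal survives rescaling.

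**The formulas carry citations.** They may follow earlier reports, which cannot be checked from the document. That is a reason to keep the old sums for comparison. It does not make them areas for these sampling times.

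**Homa-islet has only slipped out of a list.** This stands. It is named in the abstract Methods and defined in 4.8.2, so the trial evidently intends to compute it. The fault is inconsistency, not removal.

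**Stronger readings.** A reader might infer that a true gain in secretion would be scored as harm, or that the β-cell claim would rest on the wrong index. The document supports neither. It sets no direction of benefit, combines no indices and makes HOMA-IR decisive nowhere. HOMA-IR is unchanged or lower if fasting glucose falls enough. SCP is in every list and rises with C-peptide. It would equally go too far to rest any β-cell conclusion on Homa-islet alone, because it rises from 36 to 46.3 when glucose alone falls from 8 to 7.

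**Conclusion.** The point holds as a formula error together with a labelling and listing fault. SG and SCP are not areas under the curve for samples at 0, 30, 60, 120 and 180 min. The 0 and 30 min values carry twice, and the 60 min value 1.33 times, their proper weight. This follows from the stated formulas and times without further assumption. The reversal of two curves (50.0 and 49.5 against 38.25 and 39.0) shows what can happen. It rests on invented profiles, and the document gives no data from which to judge how likely a reversal is in the comparison of arms.

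HOMA-IR is filed under the wrong construct by the protocol's own description of it, and three statements of the same list disagree about Homa-islet. The opposite readings of the two HOMA indices are conditional on fixed fasting glucose and on lower HOMA-IR being read as better.

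Only secondary outcomes are affected. The primary ultrasound outcome and the sample size calculation, which uses SDBG, are untouched.

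**What to change.** 1. In 4.8.2, replace the weights in both SG and SCP by 0.25, 0.5, 0.75, 1.0 and 0.5 (hours) for the 0, 30, 60, 120 and 180 min values. If comparability with earlier reports is wanted, give the present sums alongside and call them weighted sums.
2. Report HOMA-IR under insulin resistance and SG under glycaemia.
3. In the abstract Methods, the abstract Discussion and 4.8.2 (list and formula lead-in), name Homa-islet and SCP, with SCP read alongside SG, as the β-cell indices.
4. State the direction of benefit for each index.

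The cost is wording and two formulas. Every value needed is already collected at baseline and week 8. The downside is that the main SG and SCP results will not match earlier reports that used the equal-spacing formula.
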